**Figure 1 Fig1:**
[figure not shown]
**Flow diagram of study protocol.**

### Anthropometry

The determination of post-void nude body mass for the participants will be recorded on their first visit to the laboratory to allow for an accurate nutrient provision for each participant during the training intervention that are calculated relative to each participant’s body mass. Weighing of each participant’s body mass will be undertaken using a balance scale (Weylux 424, Fereday & Sons Ltd., United Kingdom), while the measurement stature will be recorded using a stadiometer (Holtain Ltd., Crosswell, UK) following a protocol described elsewhere [47]. From the collective measurements obtained above, body mass index will then be determined (kg · m^−2^).

Body fat percentage (%BF) estimates will be taken during the second laboratory visit at baseline and follow-up testing, each following 48 hours of standardized lifestyle control. These measurements will be based on BIA analysis method (BC-543, Tanita, Tokyo, Japan). This method was shown to overestimate %BF by 3 to 4% in healthy lean males and females (<15% and <25%BF, respectively) and underestimate %BF by 3 to 4% in overweight/obese males and females (>25% and >33%, respectively), in a healthy population, relative to the dual-energy X-ray absorptiometry reference method [48]. While changes in %BF are not anticipated in the current study protocol based on findings from similar investigations [11, 20], the bias in BIA measurement will be taken into consideration when interpreting or discussing any data related to %BF in the current protocol [48].

### Submaximal and maximal oxygen uptake measurements

Running economy (· km^−1^) and () measurements will be assessed for participants during the first laboratory visit during baseline and follow-up testing [49]. These tests initially require participants to run on a motorized treadmill (Ergo ELG70, Woodway, Weil am Rhein, Germany). The protocol involves a standardized five-minute warm-up that consists of jogging at a speed of 7.5 km · h^−1^, followed by a running economy test. This requires participants to run at various submaximal speeds with increments of 1 km · h^−1^ to enable a minimum of four different running speeds (8 to 11 km · h^−1^). Each running speed will consist of three-minute stages, during which expired gas, heart rate (HR) and ratings of perceived exertion (RPE) will be recorded at the final minute of each stage. Expired gas samples, HR and RPE will be obtained via the Douglas bag method, short range telemetry (Polar FT2, Kempele, Finland) and Borg’s scale (range of the scale: 6 to 20) [50], respectively. Approximately 20 minutes following the submaximal test, a run time to volitional exhaustion will be initiated to determine relative  values for participants, which is described in further detail elsewhere [47]. The criteria of the British Association of Sport and Exercise Sciences for establishing  in adult subjects will be used to ensure the attainment of 
[51]. These will include the achievement of a maximal HR within 10 beats · min^−1^ from the predicted HR maximum for participants (220 beats · min^−1^ − age), respiratory exchange ratio (RER) values of 1.1 or greater and subjective indication of volitional exhaustion on the RPE scale. The data acquired from these tests will subsequently be used to calculate the treadmill speeds required by the trial procedures (speeds that elicit 60, 70 and 75% ) by linear regression (Excel 2010, Microsoft, Redmond, Washington, United States).

### Physiological measurements

#### Hydration

During baseline and follow-up measurement days, urine samples will be collected to determine hydration via freezing point depression method, using a cryoscopic osmometer (Advanced Instruments, Inc, Norwood, Massachusetts, United States). The threshold for adequate hydration will be assumed for osmolality values ≤900 mOsm · kg^−1^
[52].

#### Expired gas sampling

The Douglas bag method (Hans Rudolph, Shawnee, Kansas, United States) will be used for expired gas analysis. A respiratory valve with a mouth piece will be attached to a 200 l Douglas bag for expired gas sampling and provided with a nose clip to participants approximately 30 seconds before sampling to remove any residual atmospheric air from the valves. The collected gas samples will then be analyzed for relative expired fractions of oxygen and carbon dioxide using a paramagnetic and infrared analyzers, respectively (Servomex, Crowborough, United Kingdom). The total volume of expired gas within the Douglas bag will subsequently be measured by a dry gas meter (Harvard Apparatus, Kent, United Kingdom), with the temperature of expired gases being collected at the time of evacuation by a thermistor probe (Grant Instruments Ltd., Cambridgeshire, United Kingdom). Calibration of equipment will be conducted prior to any measurements using gas cylinders containing specific gases with a known relative composition (N_2_ = 0%; O_2_ = 16.9%; CO_2_ = 4.93%), as validated by the manufacturer (CryoService, Worcester, United Kingdom). Each analyzer will then be validated against atmospheric air bottled within a Douglas bag. Inspired air will be measured proximally to the participants before obtaining any corresponding expired gas sample, in order to minimize bias associated with assumptions that inspired gas fractions are stable and reflective of atmospheric constants [53].

Indirect calorimetry based on calculations of oxygen consumption and carbon dioxide production from each bag will then be used to obtain measurements of RMR. The processes followed by individuals being measured and those to be applied by the researchers will follow recommendations by The American Dietetic Association related to best practice for measuring RMR [54]. The processes followed include participants arriving from an eight to 10-hour overnight fast following two days of standardized physical activity and diet in a quiet, private space with temperature controlled between 20 and 25°C. Additionally, participants will be rested in the same reclined position for five to seven minutes before steady-state conditions and measurement interval (two five-minute periods) occur.

#### Blood sampling

Venous blood samples will be obtained by venipuncture using an antecubital vein. Prior to any attainment of a blood sample, participants will be rested in a semi-supine position for 15 minutes. A 10 ml blood sample will be collected before being dispensed into two 5 ml EDTA-treated tubes (Sarstedt, Leicester, United Kingdom). The first of these tubes will be analyzed for hemoglobin concentrations by using an automated hematology analyzer (Sysmex SF-3000; Sysmex Ltd., Wymbush, United Kingdom). Thereafter, three 50 μl aliquots of blood will be removed using micro-hematocrit tubes, and subsequently centrifuged (Hawksley, Lancing, United Kingdom) to obtain hematocrit concentrations. Hemoglobin and hematocrit concentrations will then be used to determine changes in plasma volume [55]. The remaining EDTA-treated blood will then be spun for centrifugation under 2000 xg for 10 minutes at 4°C (Heraeus Primo R; Thermo Fisher Scientific, Loughborough, United Kingdom) for plasma extraction then stored at −80°C for later analysis of plasma albumin concentration utilizing an automated spectrophotometric analyzer (RX Daytona, Randox, Crumlin, Ireland). Prior to each sample analysis, a calibration will be conducted and quality control will be checked against manufacturer’s available standards. Plasma albumin content will consequently be determined from plasma albumin concentration and the change in plasma volume, as previously described [56].

#### Muscle biopsy sampling

An 80 to 100 mg muscle biopsy sample will be obtained at baseline and follow-up via needle biopsy techniques [57]. A 5 mm skin incision will be made from the lateral portion (vastus lateralis) of the thigh from the same leg at baseline and follow-up and separated by 2 to 3 cm, with the use of dominant and non-dominant legs being counterbalanced between participants. The detailed procedures for obtaining the muscle biopsy samples are reported elsewhere [47].

Once removed from the thigh, each muscle sample will be immediately immersed in liquid nitrogen and kept stored pending subsequent analysis. The obtained muscle samples will be freeze-dried and dissected free of any visible adipose, blood and connective tissue, and separated into two specimens with a scalpel. One part of the frozen muscle tissue will be used to evaluate the impact of endurance training on selected genes and proteins involved in cellular adaptive processes (such as *GLUT-4, HKII, FABPpm, PDK4, PPARδ, PGC-1α, SIRT1, AMPK, P38MAPK, P53, ERK1* and *2*) using quantitative real-time PCR and Western blotting, as previously described [58]. Another part of the frozen muscle tissue will be utilized to determine the enzyme activity of citrate synthase [59].

#### Standardization of lifestyle

Throughout the duration of the study, participants will be asked to maintain constant dietary energy intake and activity levels (no important changes in caloric intake, dietary habits or physical activity levels outside the scope of the prescribed supplements and training sessions). The prescribed exercise training is anticipated to only result in a small degree of dietary compensation by increasing the energy intake to offset the increase in energy expenditure, with no compensatory reduction in non-prescribed physical activity, particularly in view of the free-living conditions introduced by the study [60]. Over the 48 hours prior to baseline testing, a weighed dietary record and an exercise activity log will have been completed by participants. These dietary records will be analyzed using nutritional analysis software (Nutritics LTD, Dublin, Ireland) and reported as the average total daily energy intake and percentage contribution of carbohydrate, protein and fat. The exercise activity logs over the 48-hour period will be assessed to examine the mode of exercise (for example cycling, running or resistance exercise) and total minutes of activity during a given exercise session. Participants will then be required to replicate these procedures in the 48 hours preceding the follow-up testing. Alcohol abstinence will be employed throughout this period, while caffeine consumption will be permitted until 17:00 on the day preceding any testing to avoid any unnecessary side effects as a result of adverse withdrawal from caffeine consumption [61]. Moreover, three, three-day dietary records will be assessed and subsequently analyzed from participants at different intervals during the six-week training intervention period. This aims to provide a reflection of dietary intake habits between groups during the training period.

During prescribed training days, participants will be required not to perform any other structured exercise session and will be instructed to ingest a meal (breakfast or lunch, depending on the time of day) approximately two hours prior to any session, and thereafter abstain from any caloric intake prior to the commencement of the training session. Participants will also be instructed not to consume any calories outside the scope of the prescribed supplements during the designated supplement provision periods (either two hours immediately post-exercise or one hour prior to sleep and throughout the overnight period, depending on the phase of testing). A checklist will be included in Phase I and Phase II of testing to confirm supplement intake, time of ingestion and avoidance of any caloric intake outside the scope of the prescribed supplements. This is aimed to ensure adherence to the nutritional intervention intake and timing throughout the training period.

In an attempt to accurately monitor training and ultimately standardize the training load between treatments *in situ*, an exercise diary will be provided to each participant. Participants will complete the relevant information relating to the exercise session (time of day the training session was started, total duration of session) on any of the training days, which will then be verified by an electronic monitoring system that requires participants to use a key card to enter and leave the gymnasium. Once the study is completed, the exercise logs will be collected and cross-examined with the electronic monitoring system to verify adherence for each exercise session attendance, for each date and duration.

#### Environmental measurements

Ambient temperature, humidity and barometric pressure will be monitored and recorded throughout the trials using a portable weather station (WS 6730; Technoline, Germany). The latter will be used to record atmospheric pressure to allow for corrections to standard volumes during expired gas analysis.

### Sample size estimation

*A priori* sample size estimation (G*power version 3.1.7, University Düsseldorf, Düsseldorf, Germany) from data in the literature similar to the proposed work [11], revealed that a total of 24 participants are required to achieve 90% power to detect a worthwhile increase in an endurance performance () of 5.3 ml · kg^−1^ and standard deviation of 3.3 ml · kg^−1^, using a two-tailed t-test for independent means with an alpha level of 0.05. Rolling recruitment of 32 participants in each phase of testing will therefore be conducted when considering an anticipated 15% dropout rate [11, 36].

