### Experimental design

The proposed project involves two distinct phases of testing, each contrasting two nutritional interventions in a randomized investigator-participant double-blind parallel group design. The independent variable will be the precise nutritional intervention ingested following exercise in Phase I, while timing of ingestion will be the independent variable in Phase II. Specifically, those participants recruited for Phase I (n =32, approximately) of testing will receive a supplement containing carbohydrate (sucrose) plus protein (whey protein hydrolysate) at an ingestion rate of 0.4 and 0.4 g · kg BM^−1^ respectively. The second group will be a control group, whereby an ingestion of an isocaloric carbohydrate supplements will be assigned (0.8 g · kg BM^−1^). The two nutritional interventions provided in Phase II (n =32, approximately) will be identical (0.4 g · kg BM^−1^ carbohydrate +0.4 g · kg BM^−1^ whey protein hydrolysate), while the timing of intake will be manipulated. A group will ingest the carbohydrate-protein supplement immediately post-exercise and one hour later, while the overnight recovery group will receive the supplements one hour prior to sleep, and at 02:00, as an overnight nutritional intervention. The nutritional information for the supplements is provided in Table 1.

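### The sample-size figures do not agree: on the stated inputs 90% power needs 20 participants, not 24, and 32 carries a margin beyond 15% dropout that is not explained

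*Protocol article*

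**What the plan says.** The Sample size estimation section gives a complete calculation for a comparison of two means. The test is specified as "using a two-tailed t-test for independent means" "with an alpha level of 0.05", the difference is 5.3 ml per kg, and the spread is a "standard deviation of 3.3 ml" per kg. The stated result is that the calculation "revealed that a total of 24 participants are required to achieve 90% power to detect a worthwhile increase". The inputs are attributed to a published training study, and the software is named as G*Power 3.1.7.

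The recruitment target follows in the next sentence: "Rolling recruitment of 32 participants in each phase of testing will therefore be conducted when considering an anticipated 15% dropout rate". The Participants section repeats 32 per phase. The Experimental design section gives 32 as approximate and describes the two phases as "each contrasting two nutritional interventions in a randomized investigator-participant double-blind parallel group design". No allocation ratio and no rounding rule is given.

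**The concern.** The paragraph states every input needed to repeat the calculation except the allocation ratio, so a reader can check it, and the check fails. A standardised difference of 1.6 is very large, and 24 participants is more than 90% power would call for. The step from 24 to 32 also looks too large for 15% loss.

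This paragraph is the only quantitative support for the size of both phases. If its figures are inconsistent, a reader cannot tell what difference the trial was built to detect. That matters when a null result is interpreted. It also matters for justifying the number of participants asked to undergo repeat muscle biopsies.

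**Working it through.** **Inputs** (all from Sample size estimation unless noted)
- Difference 5.3, SD 3.3, in ml per kg as printed
- Two-tailed independent t-test, alpha 0.05, target power 90%
- Two parallel arms per phase (Experimental design), taken as 1:1, which is an assumption
- Dropout 15%, recruitment target 32 per phase

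**Step 1: effect size.** d = 5.3 / 3.3 = 1.606.

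**Step 2: power.** For n per arm, the t statistic has 2n − 2 degrees of freedom and noncentrality d × √(n/2). Power is the probability that |t| exceeds the two-sided 5% critical value. This exact noncentral-t method is the one G*Power uses.

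| Total N | n per arm | Noncentrality | Critical t | Power |
|---|---|---|---|---|
| 18 | 9 | 3.41 | 2.120 | 89.2% |
| 20 | 10 | 3.59 | 2.101 | 92.4% |
| 22 | 11 | 3.77 | 2.086 | 94.7% |
| 24 | 12 | 3.93 | 2.074 | 96.4% |
| 32 | 16 | 4.54 | 2.042 | 99.3% |

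The smallest balanced total for 90% power is 20, and for 95% it is 24. The stated pairing of 24 with 90% is not reproduced.

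**Step 3: can another reading recover 24 at 90%?**
- Normal approximation: 18.
- One-sided test: 16.
- Mann-Whitney efficiency adjustment (0.955 or 0.864): 20 or 22.
- Rounding of the inputs by ±0.05: 18 to 20. At the least favourable corner (5.25 and 3.35), 24 still gives 95.6%.

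None gives 24. For 24 to be the 90% answer, d must be about 1.385. That means an SD of 5.3 / 1.385 ≈ 3.83 with the difference unchanged, or a difference of 1.385 × 3.3 ≈ 4.57 with the SD unchanged. Alternatively, the intended power was 95%. The article does not distinguish these.

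**Step 4: dropout.** 24 / 0.85 = 28.2, so 29, or 30 for equal arms (12 / 0.85 = 14.1, so 15 per arm). The cruder inflation 24 × 1.15 = 27.6 gives 28. Working back from 32, 1 − 24/32 = 25%, and 32 × 0.85 = 27.2 completers.

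**Step 5: what the design delivers at about 27 completers (13 and 14).**
- If 5.3 and 3.3 are right: noncentrality 1.606 × √(13 × 14 / 27) = 4.17 on 25 degrees of freedom, power 98.0%. The difference detectable with 90% power is 1.299 × 3.3 ≈ 4.3.
- If the SD should be 3.83: noncentrality 1.385 × √(13 × 14 / 27) = 3.60, power about 93% for 5.3. The difference detectable with 90% power is 1.299 × 3.83 ≈ 5.0.

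These are figures for the unadjusted t-test. The Data analysis section plans a general linear model with baseline as covariate, for which they are only a guide.

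**The case against.** The strongest reply is that nothing here harms the trial. Twenty-four participants do give at least 90% power for the stated difference, so only the claim that 24 are required is inaccurate. Recruiting 32 and losing 15% leaves about 27, above both 20 and 24. This stands, and it limits the severity. A reader might infer that the trial is underpowered or wrongly sized. The document does not support that, because on the stated inputs both discrepancies add participants.

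The reply is also fair on dropout. The text says 32 was chosen "when considering an anticipated 15% dropout rate"; it does not state that 32 equals 24 / 0.85. Equal arms alone bring the figure to 30, the target is elsewhere called approximate, and randomization is stratified by sex. Rounding 28.2 up to a multiple of four (two sexes by two arms) gives 32. That rounding is not stated, so it is only a possible explanation, but it is enough to reject the stronger reading that 15% and 32 contradict each other. What remains is an unexplained margin.

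A third tempting reading is that 5.3 and 3.3 are certainly right and only the power or N is wrong. The mismatch shows that some figure is misreported but not which one, and the source study cannot be consulted from this document. Replacement detectable differences therefore cannot simply be written in.

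The reply does not remove the main point. A complete calculation is stated and does not reproduce. That is an error in what is printed, not detail left to a fuller protocol or analysis plan.

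**Conclusion.** The point holds as a minor to moderate reporting error. Assuming equal arms, the stated difference, SD, test and alpha need 20 participants for 90% power, against a stated 24. Put the other way, 24 gives 96.4% against a stated 90%. At least one of power, difference, SD or N is misreported.

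The dropout step is secondary: 32 exceeds the 29 or 30 that 15% loss implies, and the margin is not stated.

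The conclusion that power is ample rests on the printed inputs, which the mismatch itself puts in question. Even so, if an SD of 3.83 or a difference of 4.57 was the figure actually used, about 27 completers would still give roughly 93% power for the intended difference. No case for changing the size of the trial follows.

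**What to change.** Check the original G*Power inputs and output, then restate the paragraph so that power, difference, SD and N agree, and state the allocation ratio.
- If 5.3 and 3.3 are confirmed, say that 20 completers give 92% power and 24 give 96%. Add that 32 recruited with 15% loss (about 27 completers) give about 98% power for 5.3, or 90% power for about 4.3, by unadjusted t-test.
- If the difference or SD was misprinted, correct it and recompute these figures.
- In either case, say that 32 includes a margin beyond 15% dropout and give the reason for it.

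The cost is one look at the source calculation and one paragraph of wording. Recruitment, procedures and analysis are unaffected.

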### Data analysis

The majority of data include measurements of cardiovascular and intramuscular markers of endurance training adaptations at baseline and follow-up, and thus treatments × time interactions will be explored using a general linear model with baseline included as a covariate, to account for any baseline imbalances because of regression to the mean [62]. The majority of variables in this experiment therefore involve a single comparison between two level scores, and so will not be adjusted for multiple comparisons across the different variables. Any data that require a single comparison of two means will be tested for normality using the Shapiro-Wilk test before using an independent t-test or non-parametric equivalent to examine differences between treatment arms (for example, magnitude of change in absolute and relative  between treatments). Relationships between outcome variables will be examined using a Pearson’s product-moment correlation and any meaningful associations (r ≥0.7) between baseline, and the magnitude of response to exercise training will be further explored by post-stratification of the treatment group according to baseline status. Significance will be set at ≤0.05 and all results being reported as the mean and standard error of the mean (SEM) unless stated otherwise.

Participants will be advised at the initial trial enrollment meeting to carefully consider the required investment of time and effort involved in the current project. This will be undertaken to minimize any negative impact associated with loss to follow-up, and consequently likely withdrawal can be made prior to randomization [63]. However, any unforeseen circumstances or withdrawal resulting in loss to follow-up will be documented and reported in the final trial report. In accordance, the handling of missing data subsequent to withdrawal will be primarily approached in a complete-case analysis adjustment method, while an imputation method will be considered where appropriate [64, 65].

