**Methods/Design:**

The project involves two phases with each involving two treatment arms applied in a randomized investigator-participant double-blind parallel group design. For each treatment, participants will be required to undergo six weeks of running-based endurance training. Immediately post-exercise, participants will be prescribed solutions providing 0.4 grams per kilogram of body mass (g · kg^−1^) of whey protein hydrolysate plus 0.4 g · kg^−1^ sucrose, relative to an isocaloric sucrose control (0.8 g · kg^−1^; Phase I). In Phase II, identical protein supplements will be provided (0.4 + 0.4 g · kg^−1^ · h^−1^ of whey protein hydrolysate and sucrose, respectively), with the timing of ingestion manipulated to compare immediate versus overnight recovery feedings. Anthropometric, expired gas, venous blood and muscle biopsy samples will be obtained at baseline and following the six-week training period.

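### The treatment × time model lists baseline as a covariate when baseline is also one of the two responses; with the terms as listed, the interaction is not baseline-adjusted

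*Protocol article*

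**What the plan says.** The Abstract states that samples "will be obtained at baseline and following the six-week training period", and the Data analysis section describes the data as "measurements of cardiovascular and intramuscular markers of endurance training adaptations at baseline and follow-up". There are therefore two occasions.

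For these data the Data analysis section plans that "treatments × time interactions will be explored using a general linear model with baseline included as a covariate". It gives the covariate a purpose: "to account for any baseline imbalances because of regression to the mean". It does not name the response variable, and it does not say whether baseline enters as a main effect only or is also crossed with time.

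The same section plans an independent t-test, or a non-parametric equivalent, where two means are compared. Its example is the "magnitude of change in absolute and relative" value of the main fitness measure. That test has no baseline term.

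The Experimental design section describes two phases, "each contrasting two nutritional interventions in a randomized investigator-participant double-blind parallel group design".

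**The concern.** A treatment × time interaction on two occasions needs baseline in the response column. Once it is there, using the same number as a covariate is redundant or consequential, depending on a term that the sentence does not mention. The sentence promises adjustment for baseline imbalance, yet the terms it lists do not deliver it.

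Two analysts who follow this sentence in good faith can get different estimates, standard errors and p-values from the same data. The model covers most cardiovascular and intramuscular markers, which the section on the approach to the research questions names as primary outcomes. With 32 recruited per phase and 24 required, arms are about 12 to 16 if allocation is 1:1 (the ratio is not stated). Randomisation is stratified by sex only. Chance imbalance in a baseline value is realistic at that size, so it matters whether the model adjusts for it.

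**Working it through.** The plan gives no figure for this analysis, so there is none to reproduce. The sample size section is used only for arm size.

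**Inputs from the document:** two occasions, two parallel arms per phase, two-sided alpha of 0.05, 24 to 32 participants per phase.

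**Assumptions, not in the document:** 1:1 allocation; equal SD at both visits; baseline to follow-up correlation r between 0.3 and 0.9; SD of 6 and mean of 40 where simulated data are used.

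**Step 1, algebra.** Let y0 be baseline and y1 follow-up. The interaction is the between-arm difference in mean (y1 − y0). A main-effect term β·y0 contributes the same amount at both occasions, so in the within-person contrast β·y0 − β·y0 = 0. The estimate is the raw difference in mean change, whatever β is. If baseline is also crossed with time, the term γ·y0 stays in the contrast, and the interaction becomes the treatment coefficient from a regression of change on treatment and baseline. That coefficient is identical to the one from follow-up on treatment and baseline.

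**Step 2, numerical check.** One simulated data set, 12 per arm, r = 0.7, with a baseline imbalance built in:

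| Model | Estimate | SE |
|---|---|---|
| Treatment × time, no covariate (within-person) | −2.377 | 2.010 |
| Treatment × time + baseline main effect (mixed model) | −2.377 | 1.970 |
| t-test on change | −2.377 | 2.010 |
| Treatment × time + baseline × time (within-person) | −1.213 | 2.044 |
| Follow-up on treatment + baseline | −1.213 | 2.044 |

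The main-effect covariate shifts the standard error slightly and leaves the estimate unchanged. Crossing baseline with time reproduces analysis of covariance exactly (p = 0.559 for both).

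**Step 3, sensitivity to imbalance.** With a baseline difference D between arms and no treatment effect, the expected change-score difference is −(1 − r)·D. For D = 3:

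- r = 0.5: −0.5 × 3 = −1.5
- r = 0.7: −0.3 × 3 = −0.9
- r = 0.9: −0.1 × 3 = −0.3

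Simulation (12 per arm, SD 6, 4,000 trials per setting) gave −1.46, −0.88 and −0.28. The corresponding figures for analysis of covariance were 0.02, −0.01 and 0.02.

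**Step 4, precision.** In units of the common variance, the change score has variance 2(1 − r) and the analysis-of-covariance residual has 1 − r². The ratio is 2(1 − r)/[(1 − r)(1 + r)] = 2/(1 + r). The last column is the power of a valid change-score test, 16 per arm, for an effect that has 80% power under analysis of covariance (noncentral t; 29 degrees of freedom for analysis of covariance, 30 for the change score).

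| r | 2/(1 + r) | Power of change score |
|---|---|---|
| 0.3 | 1.54 | 62% |
| 0.5 | 1.33 | 68% |
| 0.7 | 1.18 | 73% |
| 0.9 | 1.05 | 78% |

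This table ignores the small cost to analysis of covariance of estimating the slope when baselines differ by chance. The simulations at 12 per arm include that cost. With no systematic imbalance and a true effect of 5.3, power was 54% against 64% at r = 0.5, 76% against 81% at r = 0.7, and above 99% for both at r = 0.9.

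**The case against.** The strongest reply is that the text never limits baseline to a main effect. In a repeated-measures general linear model a between-person covariate is fitted to each within-person contrast, so crossing with time is part of the model, and the interaction is then exactly analysis of covariance. The wording can also be read as shorthand for that analysis: the purpose given is the usual reason for it, and the section goes on to call most variables a single comparison of two scores. A journal article might leave the coding of the model to a fuller document. All of this stands as far as it goes. A reader therefore cannot conclude that the planned test is unadjusted; that is one reading of the sentence.

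Two further inferences are tempting and are not supported.

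- **Inflated type I error.** A rate of roughly 7 to 8% at r of 0.3 to 0.5 appears only if the two rows per person are stacked and treated as independent. Nothing in the article says that. With a proper within-person error term the unadjusted reading is the change-score t-test, which held about 4.9% at r of 0.3 and 0.5.
- **Unusable time effect.** An uncentred baseline crossed with time would put the time coefficient at a baseline of zero. But the article plans no test of time alone, and centring baseline would resolve it.

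The reply does not remove the point. The article does more than stay silent on coding: it names an interaction, a covariate and a purpose, and the named terms serve that purpose only with a further term that is not named. The t-test on change does not settle the reading either, since it is itself unadjusted.

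**Conclusion.** The concern holds as a badly fixed model, not as a demonstrated analysis error. With the terms as listed, the interaction equals the unadjusted difference in mean change and does not account for baseline imbalance. With an unstated baseline × time term, it does.

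The unadjusted reading is valid over randomisation. Its costs are that the estimate shifts by −(1 − r) per unit of chance imbalance and that its variance is 5% to 54% larger over r from 0.9 down to 0.3. Power falls to between 78% and 62% where analysis of covariance would have 80%. These sizes rest on equal SDs and on an assumed r. The article gives no correlation, and if r is near 0.9 for a marker, the loss for that marker is small.

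The wording should be corrected before analysis, because it governs most outcome variables and otherwise leaves the choice of model open until the data are in hand.

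**What to change.** Replace the sentence in the Data analysis section with wording such as: for each variable measured at baseline and follow-up, the follow-up value is the response; the terms are treatment and the baseline value of the same variable; the treatment coefficient, with its confidence interval, is the between-arm effect. Drop the time factor and the interaction, and report within-arm change descriptively. State that this model, not the t-test on change, provides the between-arm comparison for these variables.

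This serves the plan's own stated aim under every reading of the current text. It costs one or two sentences and needs no change to data collection or sample size. The Trial status section reports Phase I recruiting and Phase II not yet started, so on the article's account the change can be made before analysis.
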